#### 7.2.4 Definition of Secondary Outcome Measures

The secondary outcomes are defined below and will be analyzed for the ITT population only.

The following are considered the key secondary outcomes and will be analyzed by the DSC:

1. Engagement in MOUD at 7 days
2. Engagement in formal addiction treatment at the 30 days
3. Engagement in MOUD at the 30 days
4. Self-reported days of illicit opioid use (past 7 days) measured by TLFB methods at 7 days
5. Self-reported days of illicit opioid use (past 7 days) measured by TLFB methods at 30 days

##### 7.2.4.1 Engagement in MOUD at 7 days

Engagement in MOUD is defined as follows:

- 1) A participant **is engaged** in MOUD at 7 days if the following is true:  
The participant self-reports taking any of methadone (ETP.ETMETH = Yes), buprenorphine (ETP.ETBUP = Yes), or naltrexone (ETP.ETNALTR = Yes) and **at least one** facility the participant reported being in treatment at verifies any of methadone (ETF.ETMTD = Yes), buprenorphine (ETF.ETBUP = Yes), or naltrexone (ETF.ETNAL = Yes).
- 2) A participant **is not engaged** in MOUD treatment at 7 days if one of the following are true:
  - a) The participant self-reports not taking MOUD (ETP.ETMETH = No and ETP.ETBUP = No and ETP.ETNALTR = No).
  - b) The participant self-reports taking MOUD (ETP.ETMETH = Yes or ETP.BUP = Yes or ETP.ETNALTR = Yes) and all facilities are contacted and report the participant as not taking MOUD (ETP.ETMETH = No and ETP.BUP = No and ETP.ETNALTR = No).

For all other scenarios, this outcome is considered missing.

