## 3.0 INTRODUCTION

### 3.1 Background and Significance

Emergency Department (ED) initiated buprenorphine/naloxone (BUP) with referral for ongoing BUP is superior to referral alone in engaging patients with untreated opioid use disorder (OUD) in treatment at 30 days and cost effective. However, logistical barriers exist in translating research into practice. As part of CTN 0069 and CTN-0079 we have gained invaluable knowledge by conducting Implementation Science research in 4 geographically diverse, academic EDs and in, under-resourced urban and smaller community EDs, about strategies to facilitate BUP initiation in the ED. Specific logistical barriers to uptake, adoption and patient success include; (1) lack of DATA 2000 waivers among Emergency Providers (EPs), (2) prior-authorization requirements by insurers, (3) patient lack of insurance, (4) patient transportation limitations, and (5) lack of prompt access to and availability of community providers and opioid treatment programs (OTPs) to enroll patients in treatment within 72 hours. New BUP formulations such as the extended-release injectable BUP (CAM2038, XR-BUP) hold promise in addressing many of these barriers more effectively than SL-BUP by treating the patients' symptoms for up to 7 days thereby providing adequate treatment while logistical barriers are addressed. As part of the NIH's HEAL initiative's efforts to increase access to medications for OUD (MOUD) in general medical settings, we propose ED-INNOVATION (**E**mergency **D**epartment-**I**nited bupre**N**orphine **V**alida**T**ION Trial **N**etwork) to rapidly expand access to ED-initiated BUP, through dissemination and implementation strategies to approximately 30 EDs throughout the U.S., leveraging the Implementation Facilitation (IF) techniques developed in CTN 0069 and CTN 0079 and resources we have developed in conjunction with NIDA (<https://www.drugabuse.gov/ed-buprenorphine>) and with the ACEP E-QUAL Network Opioid Initiative (<https://www.acep.org/administration/quality/equal/e-quality-opioid-initiative/>). After sites achieve competence in both formulations of ED-initiated BUP, we will conduct a large pragmatic trial comparing XR-BUP with SL-BUP in ED patients with untreated OUD.

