#### **7.2.4.2 Engagement in formal addiction treatment at 30 days**

This variable is defined in the same manner as specified for the primary outcome in Section 7.2.4.1 (engagement in formal addiction treatment at 7 days).

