#### **7.2.4.3 Engagement in MOUD at 30 days**

This variable is defined in the same manner as specified in Section 7.2.4.1 for engagement in MOUD at 7 days.

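### Limb 2b of the not-engaged-in-MOUD definition (SAP 7.2.4.1) cannot be met as written, so MOUD claims that every facility refutes would be coded as missing at Day 7 and Day 30

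*Combined protocol and SAP*

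**What the plan says.** SAP 7.2.4.1 sorts participants into three classes for MOUD at Day 7. The SAP's list of eCRFs identifies ETP as the patient form and ETF as the facility form.

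- **Engaged (criterion 1):** the participant reports at least one of the three drugs on ETP, and at least one named facility "verifies any of methadone (ETF.ETMTD = Yes), buprenorphine (ETF.ETBUP = Yes), or naltrexone (ETF.ETNAL = Yes").
- **Not engaged, limb 2a:** the participant answers No on ETP to all three drugs.
- **Not engaged, limb 2b, first half:** "The participant self-reports taking MOUD (ETP.ETMETH = Yes or ETP.BUP = Yes or ETP.ETNALTR = Yes").
- **Not engaged, limb 2b, second half:** "all facilities are contacted and report the participant as not taking MOUD (ETP.ETMETH = No and ETP.BUP = No and ETP.ETNALTR = No").
- **Default:** "For all other scenarios, this outcome is considered missing".

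For Day 30 MOUD, SAP 7.2.4.3 says: "This variable is defined in the same manner as specified in Section 7.2.4.1 for engagement in MOUD at 7 days". SAP 7.2.4.2 defines 30-day engagement in formal addiction treatment as "specified for the primary outcome in Section 7.2.4.1", but that section holds the MOUD rule. The primary-outcome definition is in 7.2.1.

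SAP 7.2.5.1 and 7.2.5.3 send both MOUD outcomes to the weighted GEE of 7.2.2. SAP 7.2.4 lists both among the five key secondary outcomes.

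**The concern.** In the second half of limb 2b, the words describe the facilities' answer but the fields record the patient's answer. If the code follows the fields, limb 2b is empty. A participant who claims MOUD and is contradicted by every facility then meets neither criterion 1 nor limb 2a and falls to the missing default.

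These participants are confirmed non-engagers under the rule's evident intent. Removing them takes failures, and only failures, out of the denominator. Each arm's MOUD engagement rate is then overstated at both time points, and the loss depends on the outcome itself, which the missing-at-random assumption in SAP 7.2.7 does not cover. If the code follows the words instead, the outcome is right, but the choice has been left to the programmer of an open-label trial.

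**Working it through.** **1. Can limb 2b be met?** Take one facility and complete forms. Each form has three Yes/No drug fields, so there are 2³ = 8 patterns per form and 8 × 8 = 64 combinations.

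| Patient form | Facility form | Combinations | As written | With ETF fields in 2b |
|---|---|---|---|---|
| All No | Any | 1 × 8 = 8 | Not engaged (2a) | Not engaged (2a) |
| At least one Yes | At least one Yes | 7 × 7 = 49 | Engaged | Engaged |
| At least one Yes | All No | 7 × 1 = 7 | Missing | Not engaged (2b) |

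As written, 2b is met in 0 of 64 combinations. With facility fields it is met in 7, which are exactly the refuted claims. The other 57 do not change. Limb 2b also names ETP.BUP where criterion 1 and limb 2a name ETP.ETBUP. Treating these as two separate fields does not help, because both halves of 2b use ETP.BUP.

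**2. Effect on an arm's rate.** The documents give no figure for MOUD engagement, so there is none to reproduce. Let p be the verified share among participants evaluable under the intended rule, and r the share who claim MOUD and are refuted by every facility. Literal coding removes r from the denominator and nothing from the numerator:

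reported rate = p / (1 - r)

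For illustration, p is set to the planning values for the primary outcome in SAP 10.2 (45% SL-BUP, 53% XR-BUP). The values of r are assumptions.

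| r | p = 45% | p = 53% |
|---|---|---|
| 2% | 0.45/0.98 = 45.9% | 0.53/0.98 = 54.1% |
| 5% | 0.45/0.95 = 47.4% | 0.53/0.95 = 55.8% |
| 10% | 0.45/0.90 = 50.0% | 0.53/0.90 = 58.9% |
| 15% | 0.45/0.85 = 52.9% | 0.53/0.85 = 62.4% |

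**3. Effect on the contrast.** With no refuted claims, the difference is 8.0 points and OR = (0.53 × 0.55)/(0.45 × 0.47) = 1.378.

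| r in XR-BUP | r in SL-BUP | Difference | OR |
|---|---|---|---|
| 5% | 5% | 8.4 points | 1.402 |
| 10% | 5% | 11.5 points | 1.592 |
| 5% | 10% | 5.8 points | 1.262 |

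The contrast can move up or down, depending on which arm has more refuted claims.

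**4. Do the weights repair it?** In SAP 7.2.2 the weights come from a logistic model on arm, site, age, gender, race, ethnicity and insurance, with prior engagement still a placeholder and the Day 7 outcome added for Day 30. Participants with the same covariates get the same weight. Within such a group the reported rate is still that group's p/(1 - r). Weighting changes how groups are combined, not the inflated rate inside each one. The missing-not-at-random sensitivity analysis in SAP 7.2.7 is optional.

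**The case against.** The strongest reply is that the intent is plain and the text is not final. The words of 2b name the facilities, criterion 1 in the same section uses ETF fields, and the parallel primary-outcome rule in SAP 7.2.1 uses ETF.ETENGAGE = No. The slip ETP.BUP also points to a drafting error. SAP 14.3 calls the RCT analyses a first draft, and Exhibit 5 reserves version 4.0 for finalizing them before lock. All of this stands. It makes the bias conditional on literal coding, but it does not make the written rule usable.

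Three stronger readings are tempting, and the documents do not support them.

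- **That nobody can be classed as not engaged.** Limb 2a works. Only 2b is empty.
- **That the error favours XR-BUP.** A reader might argue that the weekly depot, described in Protocol 3.1 as treating patients' "symptoms for up to 7 days thereby providing adequate treatment while logistical barriers are addressed", lets XR-BUP participants truthfully claim buprenorphine on Day 7 with no facility to confirm it. But Protocol 8.4.9 and SAP 2.2.3.2 give SL-BUP participants a prescription that runs until their follow-up appointment, so they can make the same claim. In either arm, a participant who names no facility is unverified, not refuted. A 7-day depot also says nothing about Day 30. Any false-positive rate for the comparison would rest on refuted shares chosen by the reader.
- **That 30-day formal treatment inherits the defect.** The reference in 7.2.4.2 is wrong, but the sentence names the primary outcome and describes it in parentheses, so 7.2.1 is clearly meant.

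**Conclusion.** The point holds for limb 2b. Its words and fields contradict each other, and as coded no record can satisfy it. Two of the five key secondary outcomes are affected: MOUD engagement at Day 7 and at Day 30. The primary outcome is not, because its rule uses a facility field.

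If the rule is programmed as written, each arm's rate is overstated whenever any claim is refuted by all facilities. From 45%, the overstatement is 0.9 points at r = 2%, 2.4 at 5% and 5.0 at 10%. These sizes rest on assumed values of r, a borrowed value of p and otherwise complete data. The direction and size of the effect on XR-BUP versus SL-BUP cannot be determined, because r by arm is not given.

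This is an error in an analysis rule that should be corrected before lock. It is not evidence that a biased analysis has been run.

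**What to change.** Make these changes in SAP version 4.0, before database lock:

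1. In the first half of limb 2b, change ETP.BUP to ETP.ETBUP. If the dataset holds only ETP.ETBUP, a participant who claims buprenorphine alone would otherwise fail the first half even after the second is repaired.
2. In the second half, require that all facilities listed by the participant were contacted and that each reports ETF.ETMTD = No and ETF.ETBUP = No and ETF.ETNAL = No.
3. State that the outcome stays missing when a listed facility was not reached and none verified MOUD, or when no facility was listed. A condition limited to the facilities that were contacted would be too loose: one denial plus one unreachable facility would count as not engaged, and a participant with no facility would meet it vacuously.
4. Apply the same rule at Day 30 through 7.2.4.3.
5. In 7.2.4.2, change the cross-reference from 7.2.4.1 to 7.2.1.

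The cost is a few lines of SAP text and the matching code. The facility fields are already named in criterion 1, so no new data collection is needed.

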#### 8.4.9 Interventions: Buprenorphine Induction and Discharge Instructions

Uniform BUP induction protocols will be used:

a) Standard SL-BUP:

- i. COWS  $\geq 8$ : Patients will receive 4mg of SL-BUP for a COWS score of 8-12 (mild withdrawal). After 30-45 minutes if tolerated and no unanticipated adverse reactions, an additional 4mg can be administered for a total of 8mg in the ED. Patients presenting with moderate-severe withdrawal ( $\text{COWS} \geq 13$ ) will receive an initial dose of 8mg SL-BUP. All patients will receive a buprenorphine prescription and instructions for additional BUP doses to allow for up to a dose of 12mg if needed, and for 16mg each subsequent day until their scheduled follow up appointment for ongoing MOUD.
- ii. COWS 4-7: Patients will be provided with a uniform set of instructions to guide unobserved (home) induction. They will be prescribed doses of SL-BUP to allow them to take dose up to 12mg in the 24 hours after discharge. All patients will also receive a buprenorphine prescription for 16mg each subsequent day until their scheduled follow up appointment for ongoing MOUD.

b) XR-BUP Injection with CAM2038 24 mg: Based on published data for equivalency of 16mg of SL-BUP and experience with the phase 3 trial, patients will receive a 24mg dose of injectable CAM2038 in the ED on Day 0. The patient will remain in the ED for 2-hours post injection to observe for worsening withdrawal or precipitated withdrawal as defined below in Section 9.8.

- i. SL-BUP Rescue Dose: If patient's COWS score is  $> 12$  after XR-BUP injection, a 4-8 mg dose of SL-BUP can be administered.

Patients can receive any of the ancillary medications per standard of care for specific symptoms of withdrawal. Example includes ondansetron for nausea or acetaminophen for headache.

Discharge Instruction: Participants randomized to XR-BUP will receive a wallet card with instructions for signs and symptoms of precipitated withdrawal and advice to return to the ED for immediate evaluation for the first 24 hours post dosing if precipitated withdrawal is suspected. Each ED will have a clinician on call for the study to assist in assessment and treatment.

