### **7.2 RCT Component**

#### **7.2.1 Definition of Primary Outcome Measure**

The primary outcome measure is engagement in formal addiction treatment for OUD at 7 days (Day 7). Formal addiction treatment is operationalized as those treatments consistent with the American Society of Addiction Medicine's levels of care (1 - 4) (Mee-Lee *et al.*, 2013).

The Engagement in Treatment: Patient (ETP) eCRF is where the participant self-reports whether they are in treatment for opioid use disorder on Day 7 (captured as Yes/No in the variable ETP.ETMEDTRT). If they report being in treatment, the participant then reports up to three different facilities where they received treatment on Day 7.

If a participant reports being in treatment on the ETP, the research team is expected to contact each facility listed on the ETP and complete the Engagement in Treatment: Facility (ETF) eCRF once for every facility listed on the ETP to verify the participant was in treatment. Among other questions (including whether the research team could contact and verify treatment), the ETF eCRF confirms whether the facility verified the participant was in treatment at that facility (captured as Yes/No in the variable ETF.ETENGAGE). If the facility verifies the participant was in treatment at that facility, the level of treatment the participant received at that facility is also captured (as No care received, Level I, Level II, Level III, Level IV, or Other in the variable ETF.ETCATGTR). If the facility reports a level of 'Other', they can specify further in free-text (captured in the ETF.ETCATSP variable).

The primary outcome is operationalized as follows:

- 1) A participant ***is engaged*** in formal addiction treatment at 7 days if the following is true:  
The participant self-reports being in treatment (ETP.ETMEDTRT = Yes) and at least one facility the participant reported being in treatment at verifies the participant was in treatment, at a level of Level I, Level II, Level III, or Level IV (ETF.ETENGAGE = Yes and ETF.ETCATGTR = [Level I, Level II, Level III, or Level IV]).
- 2) A participant ***is not engaged*** in formal addiction treatment at 7 days if one of the following are true:
  - a) The participant self-reports not being in treatment (ETP.ETMEDTRT = No).
  - b) The participant self-reports being in treatment (ETP.ETMEDTRT = Yes) and all facilities are contacted and report the participant as not being in treatment (ETF.ETENGAGE = No).

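### The SAP's MOUD engagement rule sets to missing a participant who reports taking MOUD but not being in treatment, and its facility-denial limb can never be met as written

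*Combined protocol and SAP*

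**What the plan says.** SAP 7.2.4.1 defines three scored routes.

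- **Engaged (limb 1):** the participant reports methadone, buprenorphine or naltrexone, and at least one "facility the participant reported being in treatment at verifies any of methadone (ETF.ETMTD = Yes" or the equivalent buprenorphine or naltrexone item.
- **Not engaged (limb 2a):** "The participant self-reports not taking MOUD (ETP.ETMETH = No and ETP.ETBUP = No and ETP.ETNALTR = No".
- **Not engaged (limb 2b):** the participant reports MOUD and "all facilities are contacted and report the participant as not taking MOUD (ETP.ETMETH = No and ETP.BUP = No and ETP.ETNALTR = No".

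The section closes with "For all other scenarios, this outcome is considered missing". SAP 7.2.4.3 applies the same rule at 30 days.

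SAP 7.2.1 says when facilities are recorded: "If they report being in treatment, the participant then reports up to three different facilities where they received treatment on Day 7". For the primary outcome it also has a limb that the MOUD rule lacks: "The participant self-reports not being in treatment (ETP.ETMEDTRT = No" is by itself sufficient for not engaged.

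Protocol 8.4.9 sends SL-BUP participants home with a buprenorphine prescription "for 16mg each subsequent day until their scheduled follow up appointment for ongoing MOUD". XR-BUP participants receive one injection on Day 0, which protocol 3.1 describes as treating symptoms for up to 7 days.

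SAP 7.2.5.1 and 7.2.5.3 analyse both MOUD outcomes with the weighted GEE of 7.2.2. SAP 7.2.7 rests on missing at random and makes a missing-not-at-random sensitivity analysis optional.

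**The concern.** A participant can still be taking buprenorphine supplied by the index ED visit on Day 7 without having linked to any clinic. If that person answers yes to buprenorphine and no to being in treatment, the rule has nowhere to put them. Within the SAP's own logic they cannot be engaged, because no facility verifies, yet they are not counted as not engaged either. They leave the denominator.

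MOUD engagement at 7 days is the first-listed key secondary outcome in SAP 7.2.4. A rule that removes only participants who failed verification raises the scored rate in whichever arm they belong to. If the arms are affected unequally, the XR-BUP versus SL-BUP comparison shifts as well.

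**Working it through.** **1. Trace the rules for each response pattern.**

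| Reports being in treatment | Reports MOUD | Facility information | Primary rule (7.2.1) | MOUD rule (7.2.4.1) as written |
|---|---|---|---|---|
| No | No to all three drugs | none | not engaged | not engaged (2a) |
| No | Yes to any | none listed | not engaged | **missing** |
| No | items not asked | none | not engaged | **missing** |
| Yes | Yes | a facility verifies MOUD | engaged, if treatment is verified at Level I-IV | engaged (1) |
| Yes | Yes | all facilities deny MOUD | depends on the facility's treatment answer | not engaged intended; **missing** as written |
| Yes | Yes | none named | missing | missing |

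Row 2 is the gap. Row 3 applies if the form skips the drug items for people who report no treatment; limb 2a is then unreachable for all of them. The documents do not give the skip pattern, but the rule fails either way. Row 5 fails because limb 2b requires at least one patient item to be Yes and then all of the same items to be No. Limb 1 uses the facility items (ETF.ETMTD, ETF.ETBUP, ETF.ETNAL), which is evidently what 2b should use.

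**2. Reproduce the plan's figure, used below as a stand-in.** No rate is given for MOUD engagement, so the primary-outcome rates in SAP 10.2 are borrowed: 45% SL-BUP, 53% XR-BUP, two-sided 0.05, 90% power, 850 per arm. The two-proportion formula gives 819 per arm, or 844 with continuity correction. Power at 850 is 91.0%. 1700/0.85 = 2000. The plan's figures are reproduced.

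**3. Bias in one arm.** If a share f of the arm is non-engaged and dropped, the engaged count is unchanged and the denominator shrinks: scored rate = p/(1-f).

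**4. Effect on the difference** (true difference 8.0 points; all shares are assumptions).

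| Dropped, SL-BUP | Dropped, XR-BUP | Scored SL-BUP | Scored XR-BUP | Difference (points) |
|---|---|---|---|---|
| 2% | 0 | 45.9% | 53.0% | 7.1 |
| 5% | 0 | 47.4% | 53.0% | 5.6 |
| 10% | 0 | 50.0% | 53.0% | 3.0 |
| 20% | 0 | 56.3% | 53.0% | -3.3 |
| 10% | 5% | 50.0% | 55.8% | 5.8 |
| 10% | 10% | 50.0% | 58.9% | 8.9 |
| 5% | 10% | 47.4% | 58.9% | 11.5 |
| 16.5% | 14.1% | 53.9% | 61.7% | 7.8 |

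The last row is 30% of the non-engaged in each arm (0.30 x 55% and 0.30 x 47%). With SL-BUP alone affected, power falls from 91% to 83%, 63% and 22% at 2%, 5% and 10%.

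**5. Do the weights help?** The Day 7 weight model in SAP 7.2.2 has arm, site, age, sex, race, ethnicity and insurance, with prior engagement still commented out. Within any covariate pattern the dropped participants are all non-engaged, so weighting restores the covariate mix but not the missing failures. A simulation with 10% of the SL-BUP arm dropped, weighting on arm and one baseline covariate, gave a weighted SL-BUP rate of 50.1% against a true 45.1%.

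**6. If ED-supplied buprenorphine should count as engagement,** the error reverses: scored rate = (p-f)/(1-f). A true 45% reads as (0.45-0.05)/0.95 = 42.1% at f = 5%, or (0.45-0.10)/0.90 = 38.9% at f = 10%.

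**The case against.** A reader might infer that the gap falls mainly on SL-BUP, inflates that arm's rate and so works against the trial's hypothesis. The take-home prescription makes SL-BUP a plausible main source at Day 7, but the documents do not support the rest. The depot acts for up to 7 days and the outcome is read on Day 7, so XR-BUP participants may also answer yes to buprenorphine. Similar shares in both arms leave the difference almost unchanged, and a larger share in XR-BUP would favour XR-BUP. If the drug items are skipped when no treatment is reported, both arms are affected.

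The size is equally open. No appointment timing, prescription fill rate or expected count is given, and a supply written only to the first appointment may be largely used up in someone who missed that appointment. At 30 days the rule is inherited, but leftover ED supply or an active depot is an unlikely cause.

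It can also be argued that calling these people non-engaged is a choice the SAP never makes. That is fair, although facility verification in limb 1 and the primary rule both point that way. Protocol 8.4.6 also allows a facility to be found from an EHR referral at Day 7, but SAP limb 1 uses only facilities the participant named.

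Finally, Exhibit 5 of the SAP calls the RCT section a first draft, to be finalised in version 4.0. That makes this the right time to correct the rule; it does not remove the gap.

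**Conclusion.** The scoring gap and the unusable limb 2b are established from the text alone. Both send participants without verified MOUD to missing, in a way that depends on the outcome and that the weighted GEE cannot repair. If the group is non-engaged, the rate in any affected arm is inflated by 1/(1-f): 0.9 points at f = 2% and 5 points at f = 10%, from a true 45%.

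For the treatment difference, neither direction nor size is known. Under the assumed shares above, the bias runs from near zero to several points either way. That rests on borrowed primary-outcome rates, on assumed shares by arm, and on treating the group as non-engaged. A firm statement that SL-BUP is favoured would go beyond the documents.

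This should be fixed before SAP version 4.0 and database lock. The primary outcome is not affected.

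**What to change.** In SAP 7.2.4.1 and 7.2.4.3:

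1. Add ETP.ETMEDTRT = No to the not-engaged limbs, matching 7.2.1. This works whichever skip pattern the form uses. Do not add a broader clause for having no facility listed: someone who reports being in treatment but names no facility should stay missing, as in the primary rule.
2. In limb 2b, replace the patient items in the facility denial with ETF.ETMTD, ETF.ETBUP and ETF.ETNAL = No.
3. Report by arm the number with self-reported MOUD and ETP.ETMEDTRT = No.
4. Add a sensitivity analysis scoring that group as engaged, so that the choice of definition is visible.

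The cost is a few lines of SAP text, a small change to the derivation code, one count by arm and one extra model run. No new data are needed.
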